### Sample size

4.1

The sample size is estimated based on a power analysis for repeated measures ANOVA including within-between interaction with 3 measuring time-points (t1, t2 and t3) and 2*2 groups (intervention vs. TAU, female vs. male). Standard parameters are set at alpha = 0.05, power = 0.95, and a clinically meaningful medium effect size *f* = 0.25. Considering an attrition rate of 30% (59), the total number of participants should be 80, with approximately 40 participants in the treatment (treatment groups of 5 to 10 participants each) and 40 participants in the control group.

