### Statistical analyses

4.2

For statistical analyses, we will use R with its graphical user interface R Studio. The significance level will be 0.05 for all analyses. An effect of at least moderate size will be considered as clinically relevant. To test our hypotheses, we will use multilevel models with primary and secondary outcome measures as dependent variables (three individual models for depression, perceived stress, and emotion recognition), and with timepoint (baseline, post-treatment, follow-up) and intervention condition (START NOW vs. TAU) including their interaction as independent variables. A significant interaction between intervention condition and time suggests a difference in symptom change depending on treatment group. In case of significant main or interaction effects, we will evaluate post-hoc contrast considering time and intervention condition. Treatment group will be added as level two in the multilevel framework.

Using multilevel models will allow to analyze data on the observational level, which provides more information in contrast to calculating change scores or using repeated measures ANOVA, increasing measurement accuracy and power. In addition, multilevel mixed models can handle missing observations and allow to examine random effects at the intercept and slope level. Furthermore, we will test model improvement when considering quadratic versus linear trends for time, random effects for time, and correlation structure between timepoints. Covariates, including participant age, gender, and post-migration stress will be added if they differ between intervention groups. On group level, possible covariates include facilitator, institution or cultural background.

To analyze perceived stress and resilience as potential mechanisms in treatment success, we will use bias-corrected bootstrap mediation models with intervention condition as predictor, change in symptoms of depression as outcome, and change in stress/resilience as mediator. Change in symptoms of depression and indicators of stress/resilience will consist of participant’s random slope for time extracted from the multilevel mixed models depending on results of the first hypothesis.

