### Limitations

5.2

One of the challenges of this project may be self-selection bias if certain refugees are more likely to volunteer for the intervention. This could affect the generalizability of the results to the wider refugee population. To reduce this bias, we offer high, but still appropriate, incentives of 20 CHF in vouchers for each assessment (t1 – t3). There also may be differences in the delivery of the intervention or usual care between facilitators. To counteract this bias, all facilitators receive extensive pre-training that provides the same content to all. Additionally, facilitators will be included as possible influences at level two in the multilevel framework.

Another limitation is the lack of blinding among participants and facilitators, a frequent cause of bias in RCTs that include non-pharmacological interventions. Known problems associated with lack of patient blinding, such as response bias with self-reported outcomes, relate primarily to studies with a predominantly explanatory aim (66). For instance, attrition rates may be simultaneously regarded as both sources of bias and outcomes influenced by the intervention (66). It is therefore important to understand and address the reasons for dropout. In multilevel models, a sub-model accounts for missing data. The selection model improves the analysis of growth curves by using logistic regressions to show how likely it is to have missing data at each time. Meanwhile, the pattern mixture approach looks at each group of missing data separately and then combines the results (67). Thereby, multilevel modeling makes use of all available information without needing to resort to list wise deletion. Another method of minimizing bias is that only well-validated questionnaires will be used during assessments.

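### Level two of the primary model is unclear and conflicts with the participant slopes used later, and the grouping of START NOW participants only is not handled, so the standard error of the arm-by-time test is not reliably fixed

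*Protocol article*

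**What the plan says.** Under Statistical analyses, each outcome is modelled with time, condition and their interaction, and data are analysed at the level of single observations. The hierarchy is then set in one sentence: "Treatment group will be added as level two in the multilevel framework".

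The term has two meanings in the article:

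- **Arm.** Statistical analyses: "A significant interaction between intervention condition and time suggests a difference in symptom change depending on treatment group".
- **Therapy group.** Sample size: "with approximately 40 participants in the treatment (treatment groups of 5 to 10 participants each) and 40 participants in the control group".

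Other statements bear on the hierarchy:

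- The mediation paragraph of Statistical analyses uses each participant's "random slope for time extracted from the multilevel mixed models".
- Model-improvement tests will cover "random effects for time, and correlation structure between timepoints", with no grouping unit named.
- "On group level, possible covariates include facilitator, institution or cultural background".
- Limitations adds that "facilitators will be included as possible influences at level two in the multilevel framework".

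The section on treatment as usual (TAU) describes no study groups and no sessions for that arm.

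**The concern.** The data have three occasions within each participant. In START NOW only, participants also sit within therapy groups: about 40 treated in groups of 5 to 10 gives 4 to 8 groups. The sentence on level two does not describe this structure, and each way of coding it has a problem.

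- If it means the arm, a random factor with two levels repeats the fixed effect of condition.
- If it means the therapy group and nothing else is added, repeated measures of one person are treated as independent given the group. That is at odds with the participant slopes needed for mediation.
- If a participant level is assumed and the therapy group enters as a random intercept, the intercept is constant over time and drops out of the change contrast. Differences between groups in change are then left in the error unmodelled.

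In none of these does the text say how TAU participants enter level two. The sentence governs the variance of the primary test in a trial that calls itself confirmatory. Left open, it also allows the model to be chosen after the data are seen.

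**Working it through.** **The plan's own figure.** Inputs from Sample size: f = 0.25, alpha 0.05, power 0.95, 3 time points, 4 cells, 30% attrition. No within-person correlation is given; rho = 0.5 is assumed. With lambda = f²·N·3/(1 − rho), df1 = 6 and df2 = 2(N − 4), the smallest N is 59, or 60 when balanced. Then 60 × 1.3 = 78, close to the stated 80, while 60/0.7 = 86. A two-group calculation with rho = 0.3 also gives 60, so the stated total does not reveal rho. Neither calculation has a clustering term.

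**Assumptions for the check.** 40 per arm, variance of one observation set to 1, rho 0.3 to 0.7. Group variance in post-baseline change (v), or the ICC, is 0, 0.05 or 0.10. The documents give none of rho, v or ICC.

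**1. Literal reading: observations within therapy groups, no participant level.**

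- Correct SE of the t2 − t1 contrast between arms, with no group differences: sqrt(4(1 − rho)/40). This is 0.224 at rho 0.5 and 0.173 at rho 0.7.
- SE from the literal model: about sqrt(4/40) = 0.316.
- Ratio: 1/sqrt(1 − rho) = 1.20, 1.41 and 1.83 at rho 0.3, 0.5 and 0.7.
- Simulation under no arm effect (4,000 runs per setting, groups of 5, 8 or 10, rho 0.5 or 0.7): model SE about 0.31 against a true SE of 0.17 to 0.27. Type I error of the arm-by-time test is 0.0% to 1.2%, so the interval is too wide.

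**2. Participant level plus a therapy-group random intercept.** Write the group effect as u, equal at t1, t2 and t3. In (t2 − t1) it becomes u − u = 0. In a balanced setting the arm-by-time test is therefore the same as with participants alone. If groups in fact differ in change, only START NOW carries the extra variance, which gives

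type I error = 2·(1 − Phi(1.96/sqrt(1 + (m − 1)·ICC/2))).

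| Group size m | ICC 0 | ICC 0.05 | ICC 0.10 |
|---|---|---|---|
| 5 | 5.0% | 6.2% | 7.4% |
| 7 | 5.0% | 6.8% | 8.6% |
| 10 | 5.0% | 7.7% | 10.4% |

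The simulation, which tests the whole interaction, gives about 5% at v = 0. For v of 0.05 to 0.10 it gives 5.0% to 10.6% at rho 0.5 and 6.6% to 12.8% at rho 0.7. The higher end at rho 0.7 is expected. The variance of individual change is 2(1 − rho) = 0.6 there, so v = 0.10 is an ICC of change of 0.10/0.70 = 0.14. At rho 0.5 it is 0.10/1.10 = 0.09.

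**3. Partially nested model with a group effect on change.** For groups of 8 (5 groups), rho 0.5 and v = 0.10, the SE is sqrt(0.05 + 0.10/5) = 0.265; the simulated true SE is 0.263. Type I error of the t2 − t1 contrast with Satterthwaite degrees of freedom is 4.6% to 6.0% over all settings.

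**4. Facilitator as a fixed covariate.** The abstract and the START NOW Adapted section describe the facilitator as the person who delivers START NOW. If TAU participants have none, the facilitator dummies sum to 1 for every START NOW participant and to 0 for every TAU participant. That sum is the arm indicator, so arm and facilitator cannot be separated.

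**The case against.** The strongest defence is that the hierarchy is loosely worded rather than wrong. Participant slopes, a correlation structure over time and random effects for intercept and slope are all mentioned, and none fits a model without participants. The word added can be read as a group layer on top of a repeated-measures model. Facilitator and institution as group-level covariates also suggest that the therapy group is meant, not the arm. This stands in part: participant effects are contradicted, not absent. A reader might infer that the primary test will lose much of its power; the documents do not support that, because it follows only if participants are in fact left out.

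Group-by-time effects are not excluded either, since random effects for time will be tested. But the grouping unit is not named, and with 4 to 8 groups a model-improvement test has little chance of retaining such an effect.

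A reader might also infer that TAU has no facilitators and that a facilitator term must absorb the treatment effect. The documents do not say the first, and a sentence under Limitations mentions usual care and facilitators together. The second holds only for fixed dummies; a random facilitator effect does not alias arm.

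The error rates depend on assumed values. With 30% attrition, groups of 10 shrink to 7 (6.8% and 8.6%) and groups of 5 to 3.5 (5.7% and 6.5%).

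Finally, degrees of freedom and cluster coding are often left to an analysis plan, so their absence alone is no fault. The point rests on the level-two statement that the article does make.

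**Conclusion.** The concern holds in a conditional form. The stated hierarchy conflicts with the participant slopes taken from the same models, its key term has two meanings, and the one-sided grouping is not dealt with. The documents do not show that the interval will be wrong, nor in which direction:

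- too wide if the sentence is followed literally;
- too narrow if participants are included but groups differ in change and only a group intercept is fitted;
- about right if participants are included and groups do not differ in change.

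Across these codings the simulated type I error ran from about 0% to about 13%. The figures rest on the assumed values of rho and of the group variance or ICC, and on balanced data. Because the choice decides the variance of the primary test, it should be settled before the data are analysed.

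**What to change.** Replace the level-two sentence with an explicit hierarchy:

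- **Level 1:** occasion (t1, t2, t3).
- **Level 2:** participant, with the within-person covariance stated.
- **Level 3:** therapy group, in START NOW only (partially nested), with each TAU participant a cluster of one. The group random effect acts on post-baseline change, not only on the intercept.

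Use Satterthwaite or Kenward-Roger degrees of freedom, because there are only about 4 to 8 groups. Keep one term for the arm and another for the therapy group throughout.

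Do not enter facilitator as a fixed covariate in the arm comparison. Describe variation between facilitators within START NOW, and state whether TAU participants have anyone in that role.

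The cost is a change of wording and slightly more modelling work. The confidence interval may be somewhat wider than from a model without a group effect on change. No new data or participants are needed.

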### Study design

3.1

The study is a confirmatory, randomized controlled trial with two arms that takes place in a monocentric, national setting and assesses effectiveness.

To evaluate feasibility, qualitative semi-structured interviews will be conducted with specialists working with refugees prior to the intervention study. These interviews will follow an inductive and explorative approach and involve staff from institutions such as asylum centers and dormitories for unaccompanied minors. To estimate the feasibility and effectiveness of this trial, specialists will be interviewed about their daily challenges, language and cultural barriers, as well as potential difficulties with the implementation and adaptation of START NOW. The inclusion of qualitative information can help to better understand how a complex intervention such as START NOW can work and aid in the adaptation process of the intervention (31).

After the conduction of these interviews, possible participants taking part in the intervention study are screened for eligibility. For those who are eligible, the study duration will be 6 months, including three assessments (shown in Figure 1): a baseline assessment (t1), a post-treatment assessment (t2), and a 12-weeks follow-up assessment (t3). In case a participant has missed a session, they will be marked as absent and the number of sessions will be taken into consideration in the data analysis. To minimize bias, participants will be randomly assigned to one of two experimental group conditions, (1) group skills training using an adapted version of START NOW, (2) TAU. Randomization should take place within 2 weeks before the intervention, after the baseline assessment (t1) has been conducted. Between t1 and t2, the intervention phase takes place over a period of 10 weeks, with one session per week for each group. The study takes place in a group setting since conducting mental health interventions via group workshops, which aim to enhance social interaction was observed to have a positive impact on participants’ mental health (19). For ethical reasons and to increase study-related commitment, participants in the control group (receiving TAU) as well as non-eligible participants will be offered the chance to receive treatment after the study concludes.

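### The mediation variables are random slopes for time that a fit test in the same section may discard, and no fallback is given

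*Protocol article*

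**What the plan says.** All of this is in section 4.2 (Statistical analyses) unless stated.

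- Fixed effects: "timepoint (baseline, post-treatment, follow-up) and intervention condition (START NOW vs. TAU) including their interaction as independent variables".
- Variance model: random effects are described as something that multilevel models "allow to examine random effects at the intercept and slope level". They then join a search: "Furthermore, we will test model improvement when considering quadratic versus linear trends for time, random effects for time, and correlation structure between timepoints". No criterion, order or default structure is stated.
- Mediation: change in symptoms and in stress or resilience is each participant's "random slope for time extracted from the multilevel mixed models depending on results of the first hypothesis".
- Models listed: "three individual models for depression, perceived stress, and emotion recognition". Resilience (CYRM-R) is not among them, although its slope is a mediator.
- Level: "The significance level will be 0.05 for all analyses".
- Section 3.1 says: "The study is a confirmatory, randomized controlled trial with two arms".
- Section 2.2 states three mediation hypotheses, linking HSCL-25, PSS-10 and CYRM-R.

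**The concern.** One paragraph leaves it to the data whether the models contain random slopes for time. The next uses those slopes as the data for every mediation analysis. If the slope for a scale is not retained, all participants share one slope within an arm, and there is no individual change value to enter into the bootstrap models. Stated hypotheses could then go unanalysed, or be analysed with a substitute chosen after the data are seen.

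There is a lesser issue. The variance model of a trial that calls itself confirmatory is chosen on the same data, and that choice feeds into the standard error of the arm-by-time comparison.

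**Working it through.** **Inputs.** From the article: three visits, 80 participants, 30% attrition (80 × 0.70 = 56 completers), level 0.05. Not in the article, so assumed: variances, correlations and the fit criterion (likelihood-ratio test at 0.05, or AIC). The plan has no figure of its own on this point to reproduce.

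**Step 1: slopes needed.** Group → stress → symptoms needs two (PSS-10, HSCL-25). Group → resilience → symptoms needs two (CYRM-R, HSCL-25). Resilience → stress → symptoms needs three.

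**Step 2: retention when only slopes are searched.** Adding a random slope adds two parameters (slope variance and intercept–slope covariance), so the statistic 2(ℓ_slope − ℓ_intercept) is referred to chi-square with 2 df. Settings: visits coded 0, 1, 2; intercept variance 0.6 and residual variance 0.4 (baseline SD 1); uncorrelated intercept and slope; 80 participants with complete data; no arm effect; 3000 simulated trials per row. With slope variance τ², the implied t1–t3 correlation is 0.6/√(1 + 4τ²).

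| Slope SD / baseline SD | t1–t3 correlation | Kept, LRT | Kept, AIC | Two slopes kept if independent (LRT²) |
|---|---|---|---|---|
| 0 | 0.60 | 3% | 9% | <1% |
| 0.14 | 0.58 | 7% | 16% | <1% |
| 0.22 | 0.55 | 22% | 38% | 5% |
| 0.32 | 0.51 | 61% | 76% | 37% |
| 0.39 | 0.47 | 87% | 94% | 76% |
| 0.50 | 0.42 | 99% | 100% | 99% |

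Two variations lower retention by LRT:
- With 56 completers it is about 5% at 0.14, 16% at 0.22, 22–51% at 0.32, 46–79% at 0.39 and 84–97% at 0.50 (ranges over variance settings).
- With N = 80 and an intercept–slope correlation of −0.4 it is 15%, 34%, 61% and 94% at 0.22, 0.32, 0.39 and 0.50.

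**Step 3: retention when correlation structures compete too.** Settings: N = 80, 30% dropout, assumed correlations (t1–t2 / t2–t3 / t1–t3) of .6/.6/.4 and .65/.65/.5, 600 trials each. A search over slopes alone (LRT) kept them in 38–47% of trials. With AR(1)-type structures as further candidates, AIC kept slopes in 8–9%; a separate 1000-trial run gave about 10%. An autoregressive term absorbs the same decay that a slope would.

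**Step 4: effect on the arm-by-time test.** Under a random intercept alone, the fitted variance of any change between two visits is proportional to 1 minus the mean correlation. For complete data:
- With .6/.6/.4 the mean is 0.533. For t1–t3 the SE ratio is √(0.467/0.60) = 0.88, so a nominal 5% test runs at about 8.4%. For t1–t2 it is √(0.467/0.40) = 1.08, about 3.4%.
- With .65/.65/.5 the mean is 0.60. For t1–t3 the ratio is √(0.40/0.50) = 0.89, about 8.0%. For t1–t2 it is √(0.40/0.35) = 1.07, about 3.6%.

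These are the figures if slopes were never fitted. After selection, in the 600-trial runs (Monte Carlo SE √(0.05 × 0.95/600) = 0.9 points):

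| Variance model | Linear time or t1–t3 contrast |
|---|---|
| Search over slopes only | 6.7–7.8% |
| Search over slopes and correlation structures | 5.5–6.0% |
| Slope always kept | 5.7–6.2% |

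The three-category interaction test (2 df) stayed at 5.0–5.7% under every covariance choice. In the complete-data runs of Step 2, the linear test after slope selection was at 4.6–5.6%.

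**The case against.** The best reply is that the article never says slopes are kept only if fit improves. It says improvement will be tested, and the mediation sentence carries no fit condition. Slope models could be fitted for mediation whatever the test shows, and a condensed article may leave fallbacks to the SAP. That reading is possible. But the mediation sentence takes its slopes from the models just described, and those are the models subject to the search. The article fixes both rules, so it needs to say which prevails. Its closing condition on the first hypothesis can be read in more than one way and does not supply a fallback. Forcing the slope in would not fully help either: with an estimated slope variance near zero, predicted slopes barely differ between participants.

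Three stronger readings might be inferred, and the documents support none of them.

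- *That slopes will usually be dropped.* Without variances or correlations this cannot be derived. In the Step 2 table they are kept in 87–99% of trials at a slope SD of 0.39–0.50.
- *That the confirmatory test does not hold its 0.05 level.* The fixed effects list timepoint as three categories, and that 2-df test is hardly affected. Even for linear time, the search as written includes correlation structures and gives a level like that of always keeping the slope.
- *That the plan includes a model that three visits cannot identify.* A random intercept, linear and quadratic effect plus residual would need 7 parameters against 6 variances and covariances. But the plan lists the time trend and random effects as separate items and never proposes a random quadratic effect.

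**Conclusion.** The point stands as a conflict between two rules in section 4.2, which can leave the mediation hypotheses without their variables. That follows from the text and needs no simulation. How often it would happen depends on slope variance that the article does not give: single-slope retention runs from about 3% to 99% over the settings shown, and joint retention is lower unless the slopes are strongly related. The joint figures assume independence; positively related slopes would survive together more often.

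The effect on the arm-by-time comparison is secondary and mild: at most about 7–8% for a linear test or t1–t3 contrast, under assumed lag-decaying correlations and a search limited to slopes. With constant correlation the level is correct. The primary comparison is not undermined. The change should be made because it is cheap and the mechanism analyses depend on it.

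**What to change.** In section 4.2, and in the SAP if there is one:

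1. Replace the search over random effects and correlation structure with one prespecified within-participant covariance. For example: visit as a three-level factor, unstructured 3×3 covariance (six parameters, all estimable from three visits), REML, Kenward-Roger or Satterthwaite degrees of freedom, and one named fallback for non-convergence. Keep the treatment-group level already planned.
2. Define the mediation variables independently of any fit test, for example as baseline-adjusted change in HSCL-25, PSS-10 and CYRM-R between named visits. State how participants missing a named visit are handled, and add CYRM-R to the listed models.

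The cost is wording only, with no new data. Against a random-intercept model (two parameters) the unstructured covariance adds 6 − 2 = 4 parameters, so the interval is slightly wider if correlation is truly constant. Change between visits also needs an explicit missing-data approach. The team should confirm beforehand that the chosen R package fits the group level, the covariance and the degrees-of-freedom method together.

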After informed consent has been given, participants will be screened for eligibility. Any participants can withdraw from the study at any time without personal disadvantages and without having to give a reason. The applicants can also decide about termination of treatment in case of protocol violations or if the applicants believe continuation in the study would be detrimental to the participants` well-being. If participants withdraw their participation prior to randomization, other eligible individuals can move up. Premature withdrawals in the group training will not be replaced after the beginning of the intervention. Relevant additional treatments (e.g., individual psychotherapy) administered to the participant upon entry to the trial or at any time during trial participation are regarded as concomitant treatments and will be documented as well as concomitant medication.

After the screening process, eligible persons will be notified by the project management through their institution about their participation opportunity. If someone is not eligible, both the institution as well as the individual will be notified online via mail. If eligible participants still wish to take part, they are randomly assigned to a group. In general, randomization will be done within each institution by randomly assigning participants to either the intervention or control group using computer algorithms. If not enough adolescents within an institution wish to participate, we will make an adjustment to the general randomization process by creating cross-institutional groups. Participants will be randomized in separate steps for each gender group. In this way, we ensure a random distribution between the intervention and control groups within each gender group and a safe environment for all participants. This is in tune with cultural norms and expectations of the target population, and this way, our results are more likely to provide important insights around cultural idioms of distress that may be gender specific (32).

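### Covariates enter only if the arms happen to differ, which in practice leaves out gender, a randomisation factor; separately, the baseline score is not used to gain precision

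*Protocol article*

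**What the plan says.** On covariates, section 4.2 (Statistical analyses) of the protocol article says: "Covariates, including participant age, gender, and post-migration stress will be added if they differ between intervention groups". It does not say how a difference is to be judged. For the group level it adds: "On group level, possible covariates include facilitator, institution or cultural background".

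On randomisation, section 3.2 (Study procedure) says: "Participants will be randomized in separate steps for each gender group". It also says: "In general, randomization will be done within each institution by randomly assigning participants to either the intervention or control group using computer algorithms". Cross-institutional groups replace this where an institution has too few participants.

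On sample size, section 4.1 uses a repeated-measures ANOVA with "3 measuring time-points (t1, t2 and t3) and 2*2 groups (intervention vs. TAU, female vs. male".

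On the model, section 4.2 fits each outcome "with timepoint (baseline, post-treatment, follow-up) and intervention condition (START NOW vs. TAU) including their interaction as independent variables". Effectiveness is read from the interaction: "A significant interaction between intervention condition and time suggests a difference in symptom change depending on treatment group". Baseline is therefore one of three outcome occasions. The article states no constraint on the arms at that occasion.

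**The concern.** The covariate rule and the design pull in opposite directions. Stratifying by gender is meant to make the arms alike on gender, and a rule that admits gender only when the arms are unlike will then leave it out. The analysis would omit a factor that was used both to randomise and to size the trial.

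For age and post-migration stress, differences between randomised arms are chance. The adjustment set is then settled by chance, after the data are seen and without a criterion, in a trial that section 3.1 calls confirmatory. Observed imbalance also says nothing about whether a variable predicts the outcome.

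Two further questions follow: whether adding such a covariate would correct the tested contrast at all, and whether the best available predictor, the HSCL-25 score at t1, is used to full effect.

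**Working it through.** **1. Gender in the plan's own figure.** Inputs from section 4.1: α = 0.05, power 0.95, f = 0.25, m = 3 occasions, k = 4 groups, 30% attrition, total 80. Not given and assumed: correlation ρ = 0.5, sphericity (ε = 1). Noncentrality λ = f²·N·m/(1 − ρ), with (k − 1)(m − 1) and (N − k)(m − 1) degrees of freedom.

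- At N = 60, λ = 0.0625 × 60 × 3/0.5 = 22.5 on 6 and 112 degrees of freedom.
- The smallest sufficient N is 59, or 60 in equal cells.
- 60 × 1.3 = 78, close to the stated 80 (60/0.7 would give 86). Read backwards, 80 × 0.7 = 56 completers have power 0.937.
- With only two groups (no gender) at ρ = 0.5, 44 would suffice. Two groups at ρ = 0.3 also need 60, but the article states four groups.

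So the stated total is consistent with gender being a design factor.

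**2. How often the rule would act.** Assumptions: 80 participants, balanced allocation within gender, 30% female, and p < 0.05 as the meaning of a difference. In 4,000 simulated allocations:

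| Covariate | Triggered |
|---|---|
| Gender | 0 of 4,000 |
| Age | 5.3% |
| Post-migration stress | 5.6% |
| Age or post-migration stress | 10.5% |

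**3. What an added covariate does to the tested effect.** A baseline covariate entered as a main effect shifts all three occasions of a participant by the same amount. With complete data it cancels out of every within-participant contrast, and condition-by-time is built from those. Random-intercept models were fitted with and without gender, age and post-migration stress (40 simulated trials per row, N = 80, ρ = 0.5). Dropout of 0.163 per visit gives 1 − (1 − 0.163)² ≈ 30% by t3.

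| Dropout | Mean shift in estimate (SD) | Largest shift (SD) | Ratio of standard errors |
|---|---|---|---|
| None | about 0 | 2.5 × 10⁻¹⁴ | 1.000 |
| About 30%, at random | 0.022 | 0.081 | 0.98–1.00 |
| About 30%, related to post-migration stress | 0.027 | 0.097 | 0.97–1.00 |

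The standard error under dropout is about 0.255, so the mean shift is about a tenth of it (0.027/0.255 = 0.11). These simulations ignore clustering by treatment group.

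**4. What the free baseline costs.** With complete data and no constraint at t1, the t2-versus-t1 interaction is the difference in mean change. In units of the outcome variance, the change score has variance 2(1 − ρ) and the baseline-adjusted outcome 1 − ρ². The ratio of adjusted to unadjusted is (1 − ρ²)/[2(1 − ρ)] = (1 + ρ)/2.

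As an illustration, power for one post-baseline contrast at an assumed standardised difference of 0.5:

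| ρ | Variance ratio | 40 per arm: change → adjusted | 28 per arm: change → adjusted |
|---|---|---|---|
| 0.3 | 0.65 | 47% → 65% | 35% → 50% |
| 0.5 | 0.75 | 61% → 73% | 46% → 58% |
| 0.7 | 0.85 | 82% → 88% | 68% → 75% |

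At ρ = 0.5 the gain is worth 1/0.75 = 1.33 times the participants. The range is 1.18 (ρ = 0.7) to 1.54 (ρ = 0.3).

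**The case against.** Much can be said for the plan.

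- **Randomisation factors.** A reader might infer that the rule discards the factors used to randomise. Only gender, of the three named covariates, is one. Institution falls under a separate sentence and is optional, not dropped. Treatment group is fixed as level two, and section 5.2 names facilitators as possible influences there. This stands, and the point is limited accordingly.
- **Effect on the interaction.** A reader might infer that covariates cannot change the tested effect. That is exact only for main effects with complete data. Under attrition the estimate moves a little, and the article does not exclude covariate-by-time terms, which would change it. This stands.
- **Little harm from the rule itself.** If main effects hardly touch the interaction, omitting gender from the present model costs almost nothing in precision. This also stands: the precision loss in step 4 belongs to the baseline question alone.
- **Baseline.** A reader might infer that baseline is ignored. It is not: it is modelled as the t1 outcome, a recognised specification that is valid under randomisation. The loss is one of efficiency. A constraint at t1 could be given in a fuller document, but the model as stated has none.
- **Power.** A reader might take 46% as the trial's power. It is not. It concerns one contrast at an assumed effect with 28 per arm, while the planned interaction has about 0.94 at 56 completers under the assumptions of step 1. The mixed model also keeps incomplete participants.

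**Conclusion.** The point holds as a cheap improvement to a stated method, not as a threat to validity. The article fixes a covariate rule that depends on the data and has no criterion. In practice it will leave out gender, although gender is built into both the randomisation and the sample size. For age and post-migration stress it leaves the model to chance, in about one trial in ten, and it does little to correct the imbalance that triggers it. The other randomisation factor, institution, is left optional.

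Separately, leaving the arms free at t1 inflates the variance of a single post-baseline contrast by a factor of 1.18 to 1.54 for ρ from 0.7 to 0.3.

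The text and the algebra are firm. The sizes rest on assumptions that the article does not supply: ρ, sphericity, a standardised difference of 0.5, the covariate effects, the share of female participants, balanced allocation within gender, and a 5% test for a difference.

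**What to change.** - Delete the rule that covariates enter only if the arms differ.
- Always include gender and institution, or the cross-institutional group where that was the unit of randomisation. Pool small institutions or fit institution as a random effect.
- Fix any further covariates, such as age and the post-migration stress score (RPMS), in advance whatever the observed balance, and state whether each enters as a main effect or also by time.
- Keep the three-timepoint model but constrain the arm means to be equal at t1. A main effect then no longer cancels exactly out of the contrast.
- Apply the same specification to the primary and secondary outcomes.

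Modelling t2 and t3 alone throughout would not fit the rest of section 4.2. The mediation analysis takes each participant's slope over time from these models, and a quadratic trend needs three occasions. If baseline-adjusted t2/t3 models are preferred, use them for the effectiveness test only and keep the three-timepoint model for the slopes.

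The cost is wording. By Table 1, the HSCL-25, the secondary outcomes and the RPMS are already collected at t1. The downside is some degrees of freedom for institution; the article does not give the number of institutions, so this cannot be sized here.
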